There are several meta-analyses showing that ACT is equally effective compared to well established evidence-based treatments (e.g., cognitive behavioral therapy; CBT) and superior to inactive control conditions (e.g., placebo or waitlist) and treatment as usual (TAU) in adults with depression, anxiety, pain, substance use and other types of psychopathology [21–24]. Moreover, in the United States, ACT is registered as evidence-based treatment for adults with chronic pain and depression [25]. Until now, less is known about the effectiveness of ACT for adolescents and young adults [26, 27]. Few studies investigated the effectiveness of ACT in adolescents and/or young adults with different types of problems, such as anorexia nervosa [28, 29], obsessive–compulsive anxiety [30], pain [31, 32], depressive symptoms [33, 34], autism spectrum disorder [35], social and school adaptation [36], social anxiety [37], posttraumatic stress [38], learning disabilities and anxiety [39], academic procrastination [40], trichotillomania [41], aggression [42] and antisocial behaviour [43]. These studies show promising effects. In addition, the effectiveness of the ACT your way intervention has recently been examined in a pilot study with 23 TAY with recurrent or chronic depression, who previously received CBT [44]. At posttreatment, 76.2% of the TAY did not meet the criteria for a depressive disorder anymore. Moreover, participants reported significant improvements in depressive symptoms, quality of life, perceived competence, and comorbid internalizing problems. In addition, the treatment drop-out was remarkably less (20.6%) compared to treatment drop-out in a CBT trial for the same target group of 12 to 21 year olds (ranging from 41 to 57%) [45]. Hence, results in terms of the effectiveness of ACT your way specifically, also seem promising. However, many of the abovementioned studies lack an adequate sample size, do not use a control group or randomisation, or are case studies. Furthermore, no research has been done in TAY with a wide range of psychological disorders, including comorbid, chronic and/or recurrent diagnoses. In addition, the cost-effectiveness of ACT in TAY has never been studied before.

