Therefore, the first aim of this study is to evaluate the effectiveness of ACT your way in TAY with a wide range of psychological disorders. In this study, ACT your way will be compared to TAU. We expect that, compared to TAU, ACT your way shows more improvements in our primary (i.e., psychological flexibility and the number of DSM-5 diagnoses) and secondary outcomes (i.e., the presence of the primary DSM-5 diagnosis, psychopathology, personality problems, global functioning, individual and societal functioning, quality of life, stress) at the short term (immediately after the intervention), but also at the long term (after six months). Furthermore, we expect more treatment satisfaction, less treatment drop-out and better treatment alliance (i.e., also secondary outcomes) of TAY since ACT your way is more attuned to their needs. The second aim is to examine the cost-effectiveness of ACT your way. We expect that ACT your way is more cost-effective than TAU, because, compared to carrying out multiple diagnosis-specific interventions, ACT your way can treat various problems at once [18].

The third aim is to investigate for whom and under what circumstances ACT you way works best by testing possible moderators (i.e., demographic characteristics [age, gender, education level and ethnicity of TAY], type and severity of problems, psychopathology of parents/caregivers, treatment expectancy and previous treatments). Moderators are baseline characteristics that interact with the type of treatment (i.e., ACT your way or TAU) to affect outcome. As most prior studies investigating the effects of ACT do not compare ACT to active treatments, the knowledge on treatment moderators is scarce. Based on existing findings, we expect that TAY with severer problems (i.e., higher baseline levels of psychopathology and/or more comorbid problems) will benefit more from ACT your way than from TAU [46–49]. Due to contrasting (e.g., [47, 50]) or insufficient findings in earlier research, no hypotheses are formulated regarding the moderating roles of demographic characteristics (age, gender, education level and ethnicity of TAY), type of problems, psychopathology of parents/caregivers, treatment expectancy and the number of previous treatments.

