### Study design and procedure

The study is designed as a multi-center, randomized controlled trial (RCT). Data will be collected in 14 Dutch and Belgian mental healthcare institutions. Within each institution, TAY meeting the inclusion/exclusion criteria, their parents/caregivers and their therapists will be asked to participate in the study. Parents/caregivers of adolescents younger than 16 will be directly involved in the study. TAY aged 16 and older will be asked first for permission to contact their parents/caregivers. If they agree, their parents/caregivers will be asked to participate in the study as well. Before enrolling in the study, written informed consent from TAY and parents/caregivers/legal representatives (for adolescents younger than 16) will be obtained. If parents/caregivers and therapists agree to participate, they will be asked for their own written informed consent as well.

In total, six multiple informant (TAY, parents/caregivers, therapist) assessments will be conducted: at baseline (T0), after 3 sessions (T1), after 6 sessions (T2), after 9 sessions (T3), at post-intervention (T4) and at 6-month follow-up (T5). Assessments will include diagnostic interviews (at T0, T4 and T5) and questionnaires (at T0 to T5). The assessments will be conducted by research assistants working at the participating institutions (e.g., master students and psychologists). Research assistants will be trained in administering the diagnostic interview and questionnaires. The TAY will receive a 30 euro gift card as a reward (5 euros per assessment). After the baseline assessment (T0), TAY will be randomly assigned to either the ACT your way or TAU condition using a computer generated block design. At each institution, five participants will be randomly allocated to the ACT your way condition and five participants will be randomly allocated to the TAU condition (blocksize = 10). See Fig. 1 for an overview of the study design.

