#### Treatment as usual

TAU can also be carried out both individually as in groups and will consist of a broad range of different psychological interventions, such as CBT, parent counselling, emotion regulation training, running therapy, or psychodynamic therapy. Therapists of the participating mental health care institutions decide what intervention(s) are most suitable to be carried out as TAU. We expect that in most cases, similar to ACT your way, TAU will also consist of weekly sessions. However, in the few cases that this is not possible, it is also acceptable to have bi-weekly sessions within TAU. If TAU is carried out bi-weekly, the T1, T2, T3 and T4 will take place after 2, 4, 6 and 8 sessions, respectively. We choose this option as then both in the ACT your way as TAU condition, the assessments will take place approximately around the same time.

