#### Secondary outcomes

The *presence of the primary DSM-5 diagnosis* will also be measured with the SCID-5-Junior [71] at T0, T4 and T5.

*Psychopathology* will be assessed by means of two informants: TAY will fill out the Youth Self Report (YSR) [72] at T0, T4 and T5 and parents/caregivers will fill out the Child Behavior Checklist about their child (CBCL) [73] at T0, T4 and T5. Some questions are slightly adjusted to make them more developmentally sensitive for young adults above the age of 18 (e.g., “*I cut classes or skip school*” will be adjusted to “*I cut classes or skip school/work*”). The YSR contains 69 items and the CBCL contains 74 items that are rated on a 3-point Likert scale ranging from 0 = “*not true*” to 2 = “*very true or often true*”. The psychometric properties of the YSR and CBCL are adequate [72, 73].

A short questionnaire measuring psychopathology, which is based on the YSR, the Behavior and Feeling Survey (BFS) [74], will be administered during all six assessments to register changes in psychopathology during the intervention. The BFS contains 12 items that are rated on a 5-point Likert scale ranging from 0 = “*not*” to 4 = “*always*”. The psychometric properties of the BFS are adequate [74].

The Severity Indices of Personality Problems – short form (SIPP-SF) will be used to measure *personality problems* (i.e., degree of self-control, identity integration, responsibility, relational capacities and social concordance) at T0, T2, T4 and T5 (derived from the SIPP–118) [75]. The SIPP-SF contains 60 questions that are rated on a 4-point Likert scale ranging from 0 = “*fully disagree*” to 3 = “*fully agree*”. The psychometric properties of de SIPP-SF are adequate [76].

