The presented study design has some potential challenges that could turn into limitations if not handled properly. Hence, for each potential challenge, a solution to overcome this challenge will be discussed. First, in the current study, ACT your way will be carried out both in an individual as in a group format, making it more difficult to isolate intervention effects from treatment modality effects. We decided to carry out ACT your way both individually as in groups, as both treatment modalities have their own potential advantages. For instance, group interventions might provide more opportunities for normalization, positive peer modeling and social support, whereas within individual interventions, therapists can more easily adapt exercises and subjects to the specific wishes and needs of each client. To isolate intervention from treatment modality effects, we will perform additional analyses in which we explore possible differences between both treatment modalities (see Method section). Second, the TAU condition might be heterogeneous in content and duration, which makes it challenging to compare the effects of ACT your way with the effects of TAU. To address this challenge, we will ask all therapists in the TAU condition to write down the content and duration of each session. Subsequently, we will investigate if there are differences in duration between ACT your way and TAU. If there are differences, the duration of treatment will be added as covariate in all analyses. Third, recruiting a sample of 140 TAY in 24 months could be challenging. To reach this sample size, we will cooperate with fourteen mental health care institutions in the Netherlands and Belgium. Moreover, to promote participation, we will give TAY a 30 euro giftcard as a reward and only use online questionnaires that TAY, parents/caregivers and therapists can easily fill out at home. Last, non-response and/or drop-out can also be a potential challenge. To minimize non-response, we built a website, including a system that automatically sends research assistants weekly updates via mail, that helps research assistants to monitor the assessment progress. At the website and in the weekly updates, research assistants can easily see which questionnaires are filled out or not and which ones are planned. With the help of this website and automatic mailing system, researchers can directly react to non-response and increase the response rate of the study. To minimize measurement drop-out, we will motivate TAY to continue participating by sending them thank you emails and newsletters and handing out a 5 euro gift card after each assessment. Moreover, when participants drop out of treatment, we will still ask them to fill out the post-intervention and follow-up assessments. Furthermore, to avoid potential bias due to drop-out, all analyses will be carried out according to the intention to treat principle.

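### T1 to T3 are triggered by session counts and treatment drop-outs are promised only T4 and T5, so early stoppers lose in-treatment data needed for the mediation analyses and the T2 EQ-5D

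*Protocol article*

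**What the plan says.** Study design and procedure sets six assessments: "at baseline (T0), after 3 sessions (T1), after 6 sessions (T2), after 9 sessions (T3), at post-intervention (T4) and at 6-month follow-up (T5"). For bi-weekly TAU, the section on treatment as usual says that "the T1, T2, T3 and T4 will take place after 2, 4, 6 and 8 sessions, respectively", with the aim of keeping assessment times in the two arms close together.

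The Discussion, under potential challenges, gives the rule for drop-out from treatment: "when participants drop out of treatment, we will still ask them to fill out the post-intervention and follow-up assessments". It then relies on intention to treat to avoid bias from drop-out.

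Three parts of the plan use the in-treatment waves:
- Moderation and mediation: path analyses with mediators at T1, T2 and/or T3.
- Secondary outcomes: the EQ-5D, from which QALYs are derived, is completed by the young people at T2 as well as at T0, T4 and T5.
- Secondary outcomes: the BFS "will be administered during all six assessments to register changes in psychopathology during the intervention".

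On expected drop-out, the introduction reports from the ACT your way pilot that "the treatment drop-out was remarkably less (20.6%) compared to treatment drop-out in a CBT trial", where the range was 41 to 57%. Among its hypotheses it states: "we expect more treatment satisfaction, less treatment drop-out and better treatment alliance".

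**The concern.** A session count cannot trigger an assessment for someone who no longer attends. The drop-out rule names only the two later assessments, so nothing in the article brings T1 to T3 back for a participant who has stopped. The in-treatment data would then come mainly from those who stayed. That selection happens after randomisation, and the investigators themselves expect it to differ between arms.

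The fourth aim depends on these waves. According to Table 1, five mediator instruments (FEEL-KJ, SCS-SF, AAQ, FMPS and RSES) are given during treatment only at T2. A participant in weekly treatment who stops before session 6 therefore has no in-treatment value on any of them, and no EQ-5D value between T0 and T4. Analysing participants as randomised does not recover measurements that were never requested.

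**Working it through.** **1. Passages side by side.** Weekly treatment: T1, T2, T3 after sessions 3, 6, 9. Bi-weekly TAU: after sessions 2, 4, 6. After stopping: T4 and T5 requested, T1 to T3 not mentioned, no calendar fallback. In weekly treatment, a participant who stops after session *s* has T1 only if *s* ≥ 3, T2 only if *s* ≥ 6, and T3 only if *s* ≥ 9.

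**2. What does not depend on T1 to T3.** The Effectiveness section tests condition separately at T4 and T5, adjusted for baseline. The number of DSM-5 diagnoses is measured only at T0, T4 and T5.

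**3. The plan's sample size, as the reference point.** Inputs from the sample size section: J = 70 therapists, m = 2 per therapist, d = 0.50, ICC = 0.05, α = 0.05 (two-sided assumed).

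λ = J·d² / {4·[ICC + (1 − ICC)/m]} = 70 × 0.25 / {4 × [0.05 + 0.95/2]} = 17.5 / 2.1 = 8.33

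With F(1, 68), power is 0.812. The smallest even J that reaches 0.80 is 68, or 136 participants. The stated 140 is reproduced.

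**4. Upper bound on missing T3.** With 70 per arm, if every drop-out leaves before T3:
- ACT: 70 × 0.206 = 14.4
- TAU: 70 × 0.41 = 28.7, up to 70 × 0.57 = 39.9
- Together: 43.1 to 54.3 of 140, or 31 to 39%

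**5. Range.** The article does not say when drop-outs leave, so the share *f* leaving before a given wave is varied. Power is for an ACT–TAU difference of d = 0.5 (assumed) on a mediator at that wave among those observed. It uses a normal approximation and a design effect of 1 + (2 − 1) × 0.05 = 1.05:

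power = Φ{0.5 / √[1.05 × (1/n_ACT + 1/n_TAU)] − 1.96}

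| TAU drop-out (ACT 20.6%) | f = 1/3: missing ACT / TAU, power | f = 2/3 | f = 1 |
|---|---|---|---|
| 20.6% | 4.8 / 4.8, 0.80 | 9.6 / 9.6, 0.77 | 14.4 / 14.4, 0.73 |
| 41% | 4.8 / 9.6, 0.78 | 9.6 / 19.1, 0.73 | 14.4 / 28.7, 0.66 |
| 57% | 4.8 / 13.3, 0.77 | 9.6 / 26.6, 0.69 | 14.4 / 39.9, 0.58 |

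Example, 41% and f = 1: n_ACT = 55.6 and n_TAU = 41.3, so the standard error is √[1.05 × (0.01799 + 0.02421)] = 0.2105, and Φ(0.5/0.2105 − 1.96) = Φ(0.415) = 0.66. With nobody missing, the same approximation gives 0.82. These powers concern the effect of condition on the mediator, not the whole indirect effect.

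**The case against.** The strongest reply is that the main comparison is intact. T4 and T5 are the only effectiveness time points, and drop-outs are still asked for both. That stands, and it limits the point to secondary uses of the data. A reader might infer that the primary effectiveness result is at risk from this rule; the Effectiveness section does not support that.

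Second, the rule does not say that T1 to T3 are withheld; that only T4 and T5 are collected is an inference. This is fair, but the session trigger leads to the same result unless some other rule exists, and the article gives none.

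Third, the counts are borrowed. The 41 to 57% comes from a CBT trial in 12 to 21 year olds with the same kind of depression as the pilot, whereas TAU here is mixed care for many diagnoses at ages 15 to 25. Participants who stop after session 9 lose none of T1 to T3. This also stands: the counts are an upper bound.

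Fourth, a robust maximum likelihood estimator need not discard participants with a missing mediator, and missing-data handling may be in the analysis plan. But such an analysis relies on missingness being explained by what was observed. Stopping probably relates to the very course that goes unmeasured, so asking for the data is better than modelling their absence.

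Fifth, session anchoring is defensible for questions of mechanism, and calendar dates for stoppers would mix two clocks. That is a real cost, but the therapist's drop-out form already records the date and the number of sessions, so the analysis can take it into account.

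A reader might also infer that T4 is taken on the day a participant stops, so that TAU is assessed earlier and ACT is favoured. No section says so. The stated aim of similar timing in both arms speaks against it, and the drop-out form asks for a reason, so stopping is not equated with treatment failure.

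**Conclusion.** The point holds in a limited form. As written, participants who stop early have no route to their remaining T1 to T3 measurements. The T4 and T5 effectiveness comparisons are unaffected, and no figure in the sample size section changes. What suffers is the mediation aim, the T2 EQ-5D value and the in-treatment BFS course, through missing data that are informative and probably more frequent in TAU.

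In size, at most about 14 of 70 ACT and 29 to 40 of 70 TAU participants would lack T3. If only a third of drop-outs leave before a given wave, the figures are about 5 and 10 to 13. If TAU drop-out equals that in the pilot, the loss is the same in both arms. These figures assume that the pilot rate carries over and that the CBT trial is a usable proxy for TAU. The direction between arms rests on the protocol's own hypothesis, not on data from this trial.

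**What to change.** Reword the drop-out commitment in the Discussion so that it covers all remaining assessments, in both arms. For anyone who stops treatment, send the outstanding T1 to T3 online questionnaires at the calendar times the sessions would have reached: about weeks 3, 6 and 9 on a weekly schedule. T4 then falls at the planned end of treatment, about week 12, and T5 six months later. Name the corresponding weeks in advance for bi-weekly TAU. Leave out the therapeutic alliance and group cohesion scales, which need ongoing treatment. Keep the session triggers for those still in treatment, and record the assessment date and sessions attended at every wave.

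The cost is low. The questionnaires are already online, the study website already tracks planned assessments, and the 5 euro card for each of six assessments is already promised. The downsides are some extra burden on young people who have left treatment and some non-response among them. Waves missed in this period cannot be collected later.

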## Data Availability

The data obtained in the current study will be available from the last author, [name], on reasonable request after publication of the results on the main research questions.

## Abbreviations

ACT: Acceptance and Commitment Therapy
AFQ-Y: Acceptance and Fusion Questionnaire for Youth
ASR: Adult Self-Report
AAQ: Autonomy Adolescent Questionnaire
BFS: Behavior and Feeling Survey
CBCL: Child Behavior Checklist
CGAS: Children Global Assessment Scale
CBT: Cognitive behavioral therapy
CD: Conduct disorder
ERSQ: Emotion Regulation Skills Questionnaire – Junior
EQ-5D: EuroQol 5 Dimension Questionnaire
FMPS: Frost Multidimensional Perfectionism Scale
CCQ-S: Group Climate Questionnaire-Short
ISIQ: Individual and Societal Impact Questionnaire
VEHI: Inventory of History of Treatments
LES: Life Event Scale
OCD: Obsessive–compulsive disorder
ODD: Oppositional defiant disorder
ORS: Outcome Rating Scale
PETS: Parent Expectancies for Therapy Scale
PSS: Perceived Stress Scale
QALY: Quality adjusted life years
RCT: Randomized controlled trial
RSES: Rosenberg Self-Esteem Scale
SCS-SF: Self-Compassion Scale Short Form
SSS: Service Satisfaction Scale
SIPP-SF: Severity Indices of Personality Problems – short form
SCID-5-Junior: Structured Clinical Interview for DSM-5 Disorders—Junior
TASC: Therapy Alliance Scale for Adolescents
TPC: Therapy Procedure Checklist
TAY: Transitional-age youth
TAU: Treatment as usual
YSR: Youth Self Report
